**Null Hypothesis:**
*There is no difference in nutrition knowledge, fruit and vegetable self-efficacy, dietary habits, and biochemical data between youth who receive the combination of school-based gardening of IVFs, and WhatsApp nutrition education compared to those who receive only school-based gardening of indigenous fruits and vegetables.*

**Alternative Hypothesis:**
*There is a significant difference in nutrition knowledge, fruit and vegetable self-efficacy, dietary habits, and biochemical data between youth who receive the combination of school-based gardening of IVFs and WhatsApp nutrition education compared to those who receive only school-based gardening of indigenous fruits and vegetables.*

### Overview and study design

2.2

This research design for the study is a non-randomized intervention study (quasi-experimental study design). A non-randomized study design was selected due to some feasibility constraints and logistical challenges. This includes challenges with schools meeting the inclusion criteria, such as the requirement for arable land, access to water facilities, and the presence of agricultural and nutrition teachers. Additionally, to align with policy priorities, ensure feasibility and sustained participation, sites will be selected in collaboration with state and local education authorities as well as community leaders, making random assignment impractical.

The study will be carried out in three Southwest Nigeria states which were selected from six states in the region: Ekiti, Osun, and Ogun. There will be two arms of intervention; one group will receive the school-based gardening of IVFs, and the second group will receive both school-based gardening of IVF and WhatsApp nutrition education. This means all participants will participate in the school-based gardening program of IVFs intervention. In addition, 50% (*n* = 130) of the participants will be selected for the nutrition education based on pre-selected criteria such as access to a web-supported phone and knowledge using social media like WhatsApp. Figure 1 summarizes the flow of activities in the study.

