#### Sampling technique and sampling size

2.2.1

Our target population consists of unemployed youths, with estimates ranging between 6.8 and 35% (35–38). Since this is a first of its kind study with no prior effect size for power calculation and known prevalence of IVFs consumption among the target population, a conservative sample size calculation approach was used (39). The sample size calculation applied the population proportion of 18.8% (the percentage of the unemployed Nigerian youth at 2020) in its estimate as shown below (35, 37). The sample size of 235 was calculated at a 95% confidence level and a margin error of 5% using an online calculator (40). Using a 10% expected dropout. The sample size is approximately 260 (130 per group). The formula used is shown below:

$$n=\frac{z^{2}\times \hat{p}(1-\hat{p})}{\varepsilon^{2}}$$

Where:

n is the sample size

z score (1.96 for 95% confidence level)

ε is the margin of error (0.05)

p̂  is the population proportion (0.188)

Study participants will be selected using a multi-stage sampling technique, that will incorporate non-randomized, purposive sampling technique at the state, within the state, schools/community, and individual levels. The details below describe how the estimated sample size will be achieved with the sampling technique.

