#### Intervention plan

2.3.1

The school-based gardening component of the intervention, as illustrated in Figure 3, will kick off with a 2-day workshop among the targeted participants. This workshop will cover topics such as an introduction to IVF farming and seed production process, showcasing the best soil management practices, and nutrition and food safety education. The participants will also be introduced to digital tools in agriculture, particularly the use of virtual assistants to facilitate sustainable and efficient farming practices, streamlining workflows and revolutionizing how young farmers access expert-level advice virtually, at their convenience. They will also educate participants on agribusiness models for farming and farming-related commercial activities. After the workshop, the youths will be apportioned equal plots for farming on school farmland. Through the collaboration of the school authorities and communities, the out-of-school youths will also have plots to use on the school farmland. The participants will be provided with viable seeds and other farm equipment, such as drips, knapsacks, soil improvement materials etc. to facilitate their farming activities. This will give them the opportunity to utilize the knowledge of IVF farming learned during the workshop. The agricultural science teachers in the selected schools will supervise the new farmers’ work to support community ownership. Furthermore, participants will be provided with technical support to guide them on good soil health management using the climate-smart approach throughout the farming year. Technical support will be provided through both physical and virtual approaches. At the initial stage of transplanting, the technical support will be provided weekly and then fortnightly till the vegetables are well established. Specifically, support will be provided physically to farmers in rural or semi-urban areas who have limited access to internet facilities and electricity, ensuring compliance. In contrast, urban participants will receive support through both physical and virtual means. Leveraging virtual support technology will help save costs and reduce risks associated with city traffic.

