### Data analysis

2.5

Descriptive statistics such as frequency and percentages will be used for the socio-demographic characteristics (such as age, gender, student status, and household size) and other outcome of measures (such as knowledge retention, intervention acceptability, and nutrition-related outcomes) that are categorical variables, while mean and standard deviation will be used for the continuous variables. To assess the possibility of bias resulting from missing data, we will conduct sensitivity analyses by carrying out complete case analyses. As opined by Braun and Clarke, this will ensure the robustness and credibility of our result (61). Mixed model analyses will be used to assess the intervention’s impact on skin carotenoid levels, anthropometrics, and diet diversity score (62, 63). The mixed model analysis was chosen because it accounts for repeated measures and can effectively address issues related to missing data. In these analyses, the intervention arms will be treated as the fixed effect so that the measure’s outcome change between the school gardening-only participants and school gardening and nutrition education participants can be assessed by the coefficients or estimated using the least square means. Time and intervention arm will be included as both main effects and interaction effects. The random effect will account for variability variations between groups that might affect the response. We will control for participant’s age, gender, household size, youth status (out-of-school vs. in-school status), community, and state, by including them as covariates in the adjusted models of the mixed model analysis. Mann–Whitney U Test will be used to compare the acceptability of the nutrition intervention between the groups. The analysis will be performed using IBM SPSS (version 23), and the statistical significance will be set at *p*-value <0.05.

As described by Braun and Clarke (61), the participants’ audio (sessions responses) and video recordings (tasks) from WhatsApp engagement will be analyzed using thematic analysis. We will use inductive coding to deduce the theme directly from the data. The convergent mixed method will be used to integrate the qualitative analysis with the quantitative results. This ensures a proper understanding of how participants experienced and engaged with the intervention.

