### Barriers, constraints, and mitigation strategies

3.1

To ensure the sustainability of the intervention beyond the study period, it is crucial to secure ongoing commitment from staff and students. In addition to funding, school gardening relies on sustained participation, as interest may fade over time. To address this, we will engage agricultural teachers at the selected schools and key community leaders during the intervention to maintain the program’s momentum. Furthermore, the *Roots and Greens* curriculum will be made publicly available after the study to support the long-term use of the gardening program. The researchers acknowledge potential biases associated with a non-randomized study design, such as selection bias and reduced internal validity. However, this design was chosen to take advantage of participants already being organized into natural groups based on their access to mobile phones, which will help minimize logistical challenges. Moreover, non-randomized designs offer external validity which often closely reflect real-life settings, enabling researchers to study how interventions operate in typical community or school environments. Furthermore, we acknowledge that the purposive sampling techniques may limit generalization, however we took steps to reduce bias and promote representativeness in the sample by stratifying recruitment to ensure diversity among youth status (in-school and out-of-school), geography (urban and rural), and state representation in Southwest Nigeria. Moreover, we intentionally oversampled certain groups (e.g., out-of-school youth) to ensure sufficient coverage of otherwise hard-to-reach sub-populations. These strategies enhance the practical generalizability of the findings to similar real-world environments (72).

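### The WhatsApp share is fixed only in total, so arm is likely to track urban/rural site, and a community main effect does not take site differences in change out of the time-by-arm estimate

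*Protocol article*

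**What the plan says.** All references are to the protocol article.

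- **Allocation (2.2).** Everyone gardens. Half of the participants, 130, also receive WhatsApp education, and this half "of the participants will be selected for the nutrition education based on pre-selected criteria such as access to a web-supported phone" and familiarity with social media. The share is given for the study as a whole.
- **Eligibility for WhatsApp (2.2.2).** The criteria apply to the individual: an own or a parent's internet-enabled phone, plus internet and social-media literacy. No number or share is set per community, area type or youth status. There are six communities, one rural and one urban in each of three states.
- **Stratification (3.1).** The authors took steps to "promote representativeness in the sample by stratifying recruitment to ensure diversity among youth status", geography and state. This governs who enters the study, not who enters which arm. The same section says the groups form naturally by access to mobile phones.
- **Rural access and gardening support (2.3.1).** Technical "support will be provided physically to farmers in rural or semi-urban areas who have limited access to internet facilities and electricity", while urban participants get physical and virtual support.
- **Analysis (2.5).** The mixed model includes time, arm and their interaction. It controls for "age, gender, household size, youth status (out-of-school vs. in-school status), community, and state, by including them as covariates in the adjusted models". No community-by-time or urban/rural-by-time term is named.
- **Size (2.2.1).** "The sample size is approximately 260 (130 per group").

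**The concern.** A rule that fills one arm by phone access, in a study that deliberately mixes places with good and poor internet, tends to draw that arm from the better-connected places. Nothing in the stated rule counteracts this. If it happens, the WhatsApp arm is mostly urban and the gardening-only arm mostly rural. The arm contrast then also carries whatever differs between urban and rural sites over the study period. One such difference is written into the plan: the mode of gardening support.

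Section 3.1 relies on the adjusted model to control confounding. The question is whether the model in 2.5, as described, can do so for change over time. At stake is a claim that WhatsApp education changed skin carotenoids, anthropometry or dietary diversity when the sites would have diverged without it.

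**Working it through.** **1. The plan's own figure.** "The sample size of 235 was calculated at a 95% confidence level and a margin error of 5% using an online calculator", and "The sample size calculation applied the population proportion of 18.8"%.

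n = 1.96² × 0.188 × 0.812 / 0.05² = 234.6, rounded up to 235. With 10% dropout, 235/0.9 = 261.1 (262 rounded up), or 235 × 1.1 = 258.5 (259). The stated 260 agrees with either. This is a precision figure for a single proportion. It carries no stated power for the arm comparison, so the effects below are given in SD units.

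**2. Inputs.** From the documents: 260 participants, 130 per arm, six communities (three rural, three urban), a baseline and a post-intervention measurement, significance at 0.05. Assumed, because the documents give no figures:
- equal communities, 260/6 ≈ 43 each;
- a WhatsApp share *s* in urban communities and 1 − *s* in rural ones;
- unit variance at each visit and within-person correlation 0.5;
- an urban-rural difference in change of δ = 0.3 SD, the same in both arms;
- a two-sided test.

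**3. What a community main effect does.** With two visits, time-by-arm is the difference between arms in mean within-person change. Anything constant within a person, including a community main effect, cancels from change. The variance of change is 2(1 − 0.5) = 1, so

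SE = √(1/130 + 1/130) = 0.124 SD.

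This is the same at 50/50, 70/30, 80/20 and 90/10. The covariate neither costs precision nor removes site differences in change.

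**4. Bias under that model, with no true arm effect.** A proportion *s* of the WhatsApp arm is urban and 1 − *s* of the gardening-only arm, so

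false arm effect = δ × [s − (1 − s)] = 0.3 × (2s − 1).

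Type I error = 1 − Φ(1.96 − b/0.124) + Φ(−1.96 − b/0.124), with b the false effect.

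| Urban/rural WhatsApp share | False arm effect (SD) | Type I error |
|---|---|---|
| 50/50 | 0 | 0.05 |
| 70/30 | 0.3 × 0.4 = 0.12 | 0.16 |
| 80/20 | 0.3 × 0.6 = 0.18 | 0.31 |
| 90/10 | 0.3 × 0.8 = 0.24 | 0.49 |

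A simulation of change scores (20,000 runs, whole-number community counts) gave mean false effects of 0.12, 0.18 and 0.24 SD and type I errors of 0.16, 0.29 and 0.50. The small differences from the table come mainly from rounding participants to whole numbers.

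**5. Cost of removing the bias by analysis alone.** Adding community-by-time makes the contrast strictly within community. Information kept = 4s(1 − s), and SE = 0.124/√[4s(1 − s)].

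| Share | Information kept | Effective n of 260 | SE (SD) |
|---|---|---|---|
| 50/50 | 100% | 260 | 0.124 |
| 70/30 | 4 × 0.7 × 0.3 = 84% | 218 | 0.135 |
| 80/20 | 4 × 0.8 × 0.2 = 64% | 166 | 0.155 |
| 90/10 | 4 × 0.9 × 0.1 = 36% | 94 | 0.207 |

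With whole-number counts per community the last two SEs are 0.153 and 0.214. At 100/0 the within-community contrast cannot be estimated.

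**The case against.** **The imbalance is not documented.** This stands in part. No arm split by site is given. A parent's phone qualifies, which weakens any rural gradient. The introduction and discussion describe WhatsApp as widely used and phone ownership as growing. The remark on limited rural internet concerns delivery of gardening support and is not an eligibility rate. The study flowchart is not shown and could hold site numbers. Confounding is therefore a likely result of the stated rule, not an established fact, and both the splits and the 0.3 SD are assumptions.

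**A reader might infer that the community-adjusted comparison loses much of the 260.** The documents do not support that. In the model described, the SE of time-by-arm does not depend on the split. The effective sizes of 218, 166 and 94 belong to a model with community-by-time, which section 2.5 does not name, and even there the loss is 16% at 70/30 and becomes large only from about 80/20. Bias and precision loss are alternatives. As written, the plan is exposed to the bias.

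**Youth status.** The documents give no difference in phone access between in-school and out-of-school youths, so balance on it is only a precaution.

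**Selection bias is already acknowledged.** Section 3.1 does so in general terms, but not for arm against site, which the sponsor can control through quotas. Quotas would not remove selection on phone access within a site.

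**Quotas are detail for a fuller document.** Site numbers alone would be. The point here is that the stated allocation rule works against balance and the stated adjustment does not repair the consequence.

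**Conclusion.** The point holds as a likely confounding of arm with urban/rural site that the described adjustment would not remove from the time-by-arm estimate. It includes the difference in mode of gardening support. Its size is unknown. Under the stated assumptions the false arm effect runs from 0.12 to 0.24 SD, against an SE of 0.124 SD, so it ranges from about one to nearly two standard errors. It scales directly with the urban-rural difference in change and vanishes if that difference is zero or the shares are equal across sites. The conclusion that a community main effect leaves this contrast untouched follows from the two-visit structure and does not depend on the assumed numbers. The change is worth making but does not by itself invalidate the study. Confidence is medium, because the site split is not given.

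**What to change.** - **Section 2.2:** state that WhatsApp participants are to be half of those enrolled in each of the six communities, about 22 of 43, as a target where enough youths qualify. Aim for the same balance within in-school and out-of-school youths as a precaution. Where a community cannot reach half, keep as close as possible and record the shortfall. The eligibility criteria need no change, since phone owners are not barred from the gardening-only arm.
- **Section 2.5:** add community-by-time (or, more sparingly, urban/rural-by-time) to the adjusted model, and report the arm split by community. With shares near one half, this term costs almost no precision.

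**Cost:** a sentence in each section and a quota sheet for recruiters, with the total of 260 unchanged. More youths must be screened in rural communities to find enough who qualify. Selection on phone access and literacy within a site remains and should still be listed as a limitation.

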**Figure 1 fig1:**
[figure not shown]
Study flowchart.

#### Sampling technique and sampling size

2.2.1

Our target population consists of unemployed youths, with estimates ranging between 6.8 and 35% (35–38). Since this is a first of its kind study with no prior effect size for power calculation and known prevalence of IVFs consumption among the target population, a conservative sample size calculation approach was used (39). The sample size calculation applied the population proportion of 18.8% (the percentage of the unemployed Nigerian youth at 2020) in its estimate as shown below (35, 37). The sample size of 235 was calculated at a 95% confidence level and a margin error of 5% using an online calculator (40). Using a 10% expected dropout. The sample size is approximately 260 (130 per group). The formula used is shown below:

$$n=\frac{z^{2}\times \hat{p}(1-\hat{p})}{\varepsilon^{2}}$$

Where:

n is the sample size

z score (1.96 for 95% confidence level)

ε is the margin of error (0.05)

p̂  is the population proportion (0.188)

Study participants will be selected using a multi-stage sampling technique, that will incorporate non-randomized, purposive sampling technique at the state, within the state, schools/community, and individual levels. The details below describe how the estimated sample size will be achieved with the sampling technique.

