#### Participants recruitment

2.2.2

Youths aged 15–35 will be identified from schools (in-school youths) and communities (out-of-school youths) in the selected states mentioned above. The selection of target states was based on purposive selection, considering their commonality in the IVFs of interest. The second stage will involve the selection of participants from each of the six selected communities (one from a rural and another from an urban local government area (LGA) in each of the selected states). LGA is an administrative division within a Nigeria that functions as the third tier of government, below the national and state levels. The target rural and urban LGA will be randomly selected from each state’s list of LGAs.

The selection of target schools will be facilitated in collaboration with the leadership of the State Ministry of Education, based on pre-selected criteria that can support onsite gardening activities. These criteria include having: a piece of land suitable for farming, access to water, and either a fenced perimeter or good security measures in place. After the school is identified, the researcher will collaborate with school administrators and teachers in the selected communities to recruit eligible in-school and out-of-school youths. Out-of-school youths will be selected from the communities where the selected schools are situated to bridge the gap between the schools and the wider community, ensuring that the gardening projects are inclusive, sustainable, and community-driven. The summary of eligibility criteria for youth selection for the gardening intervention is highlighted as follows:

Be an in-school or out-school youth between 15 and 35 years.Located in the selected LGAs.Should remain enrolled in the selected school for another year while residing in the communities chosen as study sites for the in-school youth.Should reside in communities selected as study sites for another year for the out-of-school youths.

The exclusion criteria include:

Not an in or out-of-school youth located in the selected LGAs.Not within the age bracket (15–35 years).Does not have the willingness to participate in the study.

Youths that would be enrolled in the nutritional education arm of the intervention should:

Own or has a parent who owns an internet-enabled phone that can install the WhatsApp application.Have internet and social media literacy

The exclusion criteria for the nutrition education arm of the intervention are:

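### The sample size of 260 rests on the precision of a single youth unemployment rate, not on the two-arm comparison, and it is not conservative on the plan's own figures

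*Protocol article*

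**What the plan says.** Section 2.2.1 explains that a standard power calculation was not attempted: "Since this is a first of its kind study with no prior effect size for power calculation". It adds that the prevalence of consumption of indigenous vegetables and fruits is unknown, and concludes that "a conservative sample size calculation approach was used". The input is a national labour-market figure: "The sample size calculation applied the population proportion of 18.8% (the percentage of the unemployed Nigerian youth at 2020". The result is given as "The sample size of 235 was calculated at a 95% confidence level and a margin error of 5% using an online calculator", then raised ("Using a 10% expected dropout") to approximately 260, or 130 per group. The same section describes the population as follows: "Our target population consists of unemployed youths, with estimates ranging between 6.8 and 35" percent.

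Two other places bear on this. The eligibility list in section 2.2.2 opens with "Be an in-school or out-school youth between 15 and 35 years" and contains no condition on employment. The hypotheses in section 2.1 concern a contrast between arms: youths given gardening plus WhatsApp education, "compared to those who receive only school-based gardening of indigenous fruits and vegetables".

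**The concern.** The formula answers one question: how many people must be sampled at random to estimate one proportion to within 5 points? The proportion used is the unemployment rate. It is not among the seven primary outcome groups in section 2.4.1 or the secondary outcomes in section 2.4.2. The study's question is whether two arms differ in knowledge, self-efficacy, dietary habits and biochemical measures. Section 2.5 analyses carotenoids, anthropometrics and dietary diversity with a mixed model containing an arm-by-time interaction. A one-sample margin says nothing about the precision of that contrast.

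The word conservative tells the reader that the number errs on the large side. If it does not, the reader is reassured without cause. At stake is how the results are read: without a detectable difference, nobody can tell from the plan which effects a non-significant result would leave open.

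**Working it through.** **Inputs from the protocol article.** Section 2.2.1: p = 0.188, margin 0.05, z = 1.96, quoted range 6.8% to 35%, dropout 10%, 130 per group. Section 2.5: significance at 0.05, taken here as two-sided because no sidedness is given. Section 2.2.2: six communities. Completers per arm: 130 × 0.9 = 117.

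**Step 1. The plan's own figure.** n = z²p(1−p)/ε² = 1.96² × 0.188 × 0.812 / 0.05² = 234.6, so 235. This reproduces. For dropout, 235/0.9 = 261.1 and 235 × 1.1 = 258.5. Both fit approximately 260.

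**Step 2. Is 235 conservative?** The same formula with other proportions gives:

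| p | Source | n |
|---|---|---|
| 0.068 | lower end of the plan's range | 98 |
| 0.188 | value used | 235 |
| 0.35 | upper end of the plan's range | 350 |
| 0.50 | value that maximises n | 385 |

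The chosen 235 is 67% of the figure at the top of the plan's range (235/350) and 61% of the maximum (235/385). One reason given for caution is an unknown prevalence. That reason points to p = 0.5.

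**Step 3. What 117 per arm can detect, post-intervention comparison, independent participants.** In SD units at 80% power: (1.96 + 0.842) × √(2/117) = 0.366, about 0.37 SD. For assumed true differences of 0.2, 0.3, 0.4 and 0.5 SD, power is 33%, 63%, 86% and 97%. The total needed for 80% power, after 10% dropout, is 874, 389, 220 and 140 respectively. So 260 is enough for 0.4 SD and not for 0.3 SD.

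**Step 4. The planned arm-by-time contrast.** With baseline/follow-up correlation ρ, the detectable difference in change is 0.366 × √(2(1−ρ)). The plan gives no ρ, so these are assumed values:

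- ρ = 0.3: 0.366 × 1.183 = 0.43 SD
- ρ = 0.5: 0.366 × 1.000 = 0.37 SD
- ρ = 0.7: 0.366 × 0.775 = 0.28 SD

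**Step 5. Clustering, if the arms differ by community.** Average size is 235/6 = 39.2 per community, and the design effect is 1 + 38.2 × ICC. The plan gives no ICC, so these are assumed values, applied to the post-intervention comparison:

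- ICC = 0.01: design effect 1.38, and 0.366 × √1.38 = 0.43 SD
- ICC = 0.05: design effect 2.91, and 0.366 × √2.91 = 0.62 SD

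If both arms are present in every community, the loss is smaller. The article does not settle which applies.

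**Step 6. Target population.** Section 2.2.1 says unemployed youths. Section 2.2.2 admits in-school and out-of-school youths aged 15 to 35, requires in-school youths to remain enrolled for another year, and lists no employment condition. The two descriptions do not match.

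**The case against.** The authors are open that they had no effect size, and they claim no power for the comparison. The 5-point margin is never applied to an arm or to a difference. The study aim also includes feasibility, for which a formal power calculation may be less central. All of this stands, and it limits the point: no false power claim is being corrected. But it does not rescue the stated basis. A detectable difference in SD units needs no prior effect size, and the margin that is offered instead belongs to a quantity the study does not set out to estimate.

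A reader might infer several stronger things that the documents do not support:

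- *That 260 is too small.* This depends on the effect size, the correlation and the clustering, none of which the plan gives. At 0.4 SD with independent participants, 260 is more than enough.
- *That the dropout allowance falls short*, because 260 × 0.9 = 234 against 235. The article says approximately 260, so this is rounding.
- *That the study does not measure unemployment.* Socio-demographic data are collected at both time points, and the items named in section 2.5 are examples. What can be said is that unemployment is not a listed outcome.
- *That employment plays no part in eligibility.* Section 2.2.2 calls its list a summary. What can be said is that no employment criterion is listed.
- *That 260 was set by feasibility.* The feasibility reasons in section 2.2 explain the lack of randomisation and the choice of sites, not the number.

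**Conclusion.** The point holds as a fault in the quantity chosen for sizing, not in the arithmetic. The figure of 235 is correct for estimating an 18.8% proportion to within 5 points in a simple random sample. That describes no planned between-arm result, and selection here is purposive down to the individual level. The conservative label is wrong on the plan's own range, by 115 participants at 35% (350 − 235) and by 150 at 50% (385 − 235).

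The sample size is therefore unjustified for the stated hypotheses, but not shown to be inadequate. At 117 completers per arm, 80% power and two-sided 5%, the detectable difference is about 0.37 SD for independent participants in a post-intervention comparison. It is 0.28 to 0.43 SD for the arm-by-time contrast at assumed correlations of 0.7 down to 0.3, and 0.43 to 0.62 SD at assumed ICCs of 0.01 to 0.05 if the arms differ by community. The 0.37 SD figure should not be quoted without these conditions.

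**What to change.** In section 2.2.1:

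1. Delete the description of the approach as conservative, and remove the 95%/5% margin on the unemployment rate as the justification.
2. Have the authors state the actual basis for 260. Only they can supply it.
3. Choose one main outcome from the seven primary outcome groups. For it, report the difference between arms detectable with 117 completers per arm at 80% power and two-sided 5%. State whether it refers to the post-intervention comparison or the arm-by-time contrast, and give the assumed SD, baseline/follow-up correlation and ICC as ranges.
4. State whether both arms are present in each community, since this decides whether the clustering penalty applies.
5. Reconcile the target population in section 2.2.1 with the eligibility list in section 2.2.2. The document does not show which of the two is intended.

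The cost is text only, plus the decision on one main outcome. No participants are added, and the arms and planned analyses stay as they are. The stated precision will look less tidy than a 5-point margin, but it will refer to the comparison the study makes.
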